# Chinese Herbal Medicine (Yiqi-Yangyin-Jiedu Decoction) Combined With Osimertinib as First-Line Treatment in EGFR Mutation-Positive Advanced Non-Small-Cell Lung Cancer (CATLA-2): A Study Protocol for a Double-Blind Randomized Controlled Trial

**DOI:** 10.3389/fphar.2022.840889

**Published:** 2022-04-01

**Keywords:** non-small cell lung cancer, epidermal growth factor receptor, osimertinib, Yiqi-Yangyin-Jiedu decoction, Chinese medicine

## Abstract

**Background:** Epidermal growth factor receptor (EGFR) tyrosine kinase inhibitors (EGFR-TKIs) significantly improve the prognosis of non-small cell lung cancer (NSCLC) with EGFR mutation-positive. Although third-generation EGFR-TKI osimertinib is demonstrated with superior efficacy compared with first-generation EGFR-TKIs, acquired resistance to EGFR-TKIs remains the bottleneck. The Chinese herbal medicine (CHM) Yiqi-Yangyin-Jiedu decoction (YYJD) has been shown to delay acquired resistance to first-generation EGFR-TKIs in the CATLA study, but there is no high-level evidence for its effect when combined with osimertinib. This trial aims to evaluate the efficacy and safety of YYJD combined with osimertinib as first-line treatment in EGFR mutation-positive advanced NSCLC.

**Methods:** This is a double-blind, multi-center, randomized controlled trial conducted in eight hospitals in China. A total of 314 participants will be randomly assigned to the osimertinib plus YYJD group (O+YYJD) or the osimertinib plus placebo group (O+placebo). Treatment will last until disease progression or death. Patients diagnosed with advanced NSCLC harboring EGFR Ex19del or L858R will be enrolled if they are ready to take osimertinib as first-line treatment, aged 18–74 years old, and provide signed informed consent. The primary outcome is progression-free survival (PFS). The secondary outcomes include a comparison of overall survival (OS), objective response rate (ORR), disease control rate (DCR), and quality of life (QoL). The analysis will be based on intention-to-treat and per-protocol subject analysis principles.

**Discussion:** The goal of this trial is to evaluate the efficacy and safety of YYJD when added to osimertinib as first-line treatment in EGFR mutation-positive advanced NSCLC.

**Trial Registration:**
Chictr.org.cn, identifier ChiCTR1900026748

## Introduction

Non-small cell lung cancer (NSCLC) is the leading cause of cancer death worldwide (Siegel et al., 2020). Epidermal growth factor receptor (EGFR) is the most common driver gene for NSCLC, and approximately 40% of NSCLC patients in Asian populations have EGFR mutations (Gelatti et al., 2019). The most common mutation types in EGFR include exon 19 deletion (Ex19del) and exon 21 Leu858Arg (L858R), often referred to as “classical” mutations (Gazdar, 2009), which account for about 85% of EGFR mutations (Harrison et al., 2020). In addition, 12%–34% of NSCLC patients with EGFR mutations have uncommon mutations (Yang et al., 2015; Castellanos et al., 2017; Robichaux et al., 2018), which include exon 20 insertion, exon 18 G791X, exon 20 S768I, and exon 21 L861Q mutations. However, evidence on the efficacy of treatment for patients with uncommon mutations is insufficient. First-generation epidermal growth factor receptor tyrosine kinase inhibitors (EGFR-TKIs), such as gefitinib (Fukuoka et al., 2011) and erlotinib (Rosell et al., 2012), significantly improve the prognosis of advanced NSCLC patients harboring EGFR-TKI-sensitizing mutations, mainly EGFR Ex19del and L858R, when compared with traditional platinum-based chemotherapy as first-line treatment. Despite initial responses, most patients develop acquired resistance to first-generation EGFR-TKIs, and the disease will progress within 9–11 months (Fukuoka et al., 2011; Rosell et al., 2012). Third-generation EGFR-TKIs such as osimertinib have been shown to delay disease progression and prolong survival time compared to gefitinib (Soria et al., 2018; Ramalingam et al., 2020). Despite this, acquired resistance to osimertinib develops over a median of 18.9 months, so optimizing the effect of osimertinib is critical to the long-term survival of NSCLC patients.

Chinese herbal medicine (CHM) has been used in Chinese NSCLC patients treated with EGFR-TKIs for more than 10 years and has demonstrated its efficacy in delaying EGFR-TKI resistance and alleviating adverse effects in a number of clinical trials (Yang et al., 2018; Jiao et al., 2019; Tang et al., 2019). CHM contains several active compounds that interact with target proteins involved in EGFR-TKI resistance (Bing et al., 2018). Our previous multi-center, double-blind, placebo-controlled clinical trial (CATLA study) confirmed that the addition of CHM (Yiqi-Yangyin-Jiedu decoction, YYJD) to EGFR-TKI (gefitinib, erlotinib, or icotinib) significantly prolongs progression-free survival (PFS) and improves the quality of life (QoL) in NSCLC patients (Jiao et al., 2019). These trials mainly involve first-generation EGFR-TKIs. Osimertinib, as a third-generation EGFR-TKI, inhibits EGFR-sensitive mutations (Ex19del and L858R) like the first-generation EGFR-TKI. Given their similar mechanisms of action, it is reasonable to expect CHM to have clinical benefits for osimertinib as well.

The current study (CATLA-2) will determine whether the addition of CHM YYJD to third-generation EGFR-TKI osimertinib (O+YYJD) prolongs PFS compared with osimertinib plus placebo (O+placebo) in advanced NSCLC patients who have an activating EGFR mutation.

## Methods and Analysis

### Study Design

This is a multi-center, double-blind, randomized controlled trial, which will be conducted in Yueyang Hospital of Integrated Traditional Chinese and Western Medicine Affiliated to Shanghai University of Traditional Chinese Medicine, Shanghai Pulmonary Hospital Affiliated to Tongji University, Shanghai Chest Hospital Affiliated to Shanghai Jiaotong University, Guang’anmen Hospital of China Academy of Chinese Medical Sciences, First Affiliated Hospital of Guangzhou University of Traditional Chinese Medicine, First Affiliated Hospital of Tianjin University of Traditional Chinese Medicine, Affiliated Hospital of Chengdu University of Traditional Chinese Medicine, and Jiangsu Provincial Hospital of Traditional Chinese Medicine. The study aims to enroll 314 advanced NSCLC patients with EGFR mutation-positive. Patients will be randomized at a ratio of 1:1 to receive either osimertinib plus YYJD or osimertinib plus placebo. Follow-up will be conducted at baseline, 4 weeks after treatment, and every 8 weeks afterward until disease progression or death, which is evaluated according to Response Evaluation Criteria in Solid Tumors (RECIST) version 1.1. The study design is based on the Standard Protocol Items: Recommendations for Interventional Trials (SPIRIT) 2013 statement (Chan et al., 2013). The flow diagram of the study is shown in Figure 1.

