#### Drop-Out Criteria

(1) Those who do not comply during the trial have an impact on the evaluation of effectiveness and safety;(2) Those who withdraw themselves during the trial;(3) Those who combine drugs, especially drugs that have a large effect on test drugs, affect effectiveness and safety evaluation;(4) Those who withdraw from the trial, do not receive follow-up, or die before the end of the treatment course for other reasons;(5) Those with incomplete information that affects the evaluation of effectiveness and safety;

The investigators will continue to evaluate the safety after they have been dropped out.

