### Outcomes

Computed tomography (CT) or magnetic resonance (MR) imaging will be used to assess the tumor at baseline, 4 weeks after treatment, and every 8 weeks afterward until disease progression or death. Objective response is evaluated according to RECIST 1.1, established by the National Cancer Institute (NCI), and divided into the following four situations: Complete Response (CR), Partial Response (PR), Stable Disease (SD), and Progressive Disease (PD).

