#### Secondary Outcomes

(1) Overall survival (OS): calculated as the time from randomization to death due to any cause. For subjects who are lost to follow-up before death, the time of the last follow-up is used as the time of no death.(2) Objective response rate (ORR): calculated based on the effective rate of CR+PR patients.(3) Disease control rate (DCR): calculated based on the effective rate of CR+PR+SD patients.(4) Physical condition: assessed following the ECOG PS standard at the same time point of image evaluation.(5) QoL: evaluated with Functional Assessment of Cancer Therapy-Lung (FACT-L) questionnaire, Lung Cancer Symptom Scale (LCSS) and TCM syndrome score at the same time point of image evaluation. TCM syndrome score will be evaluated based on the grading scales of lung cancer symptoms required in the Guiding Principles of Clinical Research of New Chinese Medicine Treating Primary Bronchial Lung Cancer (2002 Edition) issued by the National Medical Products Administration of China.(6) Safety assessments: Participants will be asked and all adverse events (AEs) during treatment will be recorded at each visit, and all AEs reported will be analyzed. Blood, urine, and stool routine, liver function, and kidney function are tested for adverse reactions at the same time point of image evaluation and evaluated according to common terminology criteria for adverse events (CTCAE) version 5.0 (https://ctep.cancer.gov).

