### Statistical Analysis

Data analysis will follow the trial’s statistical analysis plan. All data will be processed by statistical analysis with SAS 9.4 software analysis. Two-tailed *p* values <0.05 are considered statistically significant. The analysis will follow intention-to-treat, full analysis set, and per-protocol subject principles for the evaluation of primary and secondary outcomes. The safety data set that includes all subjects who received at least one treatment after randomization will be used to evaluate safety and tolerance. Missing data will be processed with the multiple imputation method.

The baseline characteristics will be reported according to treatment groups. PFS and OS will be illustrated by the Kaplan–Meier survival curve and compared between groups using the log-rank test. The secondary outcomes will be summarized with frequency, mean, standard deviation, median, and range. At each time point, comparisons between the experimental group and the placebo group will be conducted using the Group t-test or Wilcoxon rank-sum test (for measurement data) and the rank-sum test and CMH test (for count data). Fisher’s exact test will be used to compare tumor response rates between the arms. For PFS, an adjusted Cox regression model will be used to estimate the adjusted HRs for differences between the treatment arms with the selected prognostic factors, including the center, EGFR mutation type, age, sex, EGFR-TKI drugs, smoking status, and ECOG PS.

Safety will be documented in adverse event forms and presented with descriptive statistics for each group. The frequency difference of adverse events between groups will be assessed by the chi-square test or Fisher’s exact test. For different AE severities, a rank-sum test will be performed to analyze the independent ordered multiple category data between the two groups.

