## Discussion

EGFR-TKIs are the standard first-line treatment for patients with locally advanced or metastatic EGFR-mutated NSCLC (Hanna et al., 2017; Planchard et al., 2018; Wu et al., 2019). Although the emergence of EGFR-TKIs has brought a revolutionary breakthrough in the treatment of lung cancer, the disease still progresses after 9–11 months of treatment with EGFR-TKIs (Fukuoka et al., 2011; Rosell et al., 2012). Patients with EGFR-mutated NSCLC who are initially sensitive to EGFR-TKI therapy will inevitably experience treatment failure due to secondary drug resistance, and more than 50% of them have the T790M mutation (John et al., 2018; Wang et al., 2018). The emergence of the third-generation EGFR-TKI, osimertinib, has solved this problem. The FLAURA study shows that the median PFS of patients treated with osimertinib is as high as 18 months, and its first-line treatment significantly prolongs OS to 38.6 months (Soria et al., 2018; Ramalingam et al., 2020). Therefore, osimertinib is the first choice for first-line treatment in EGFR mutation-positive advanced NSCLC. However, resistance and toxicities of osimertinib have become new challenges. Osimertinib resistance mechanisms include EGFR C797S mutation and MET gene amplification (Kim et al., 2015; Planchard et al., 2015). The toxic and side effects of osimertinib significantly affect the quality of life of patients with NSCLC and even lead to the cessation of treatment (Khozin et al., 2017).

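### The stated follow-up ends at progression, but overall survival needs follow-up to death, and nothing shown bridges the two; read literally, OS would be censored informatively

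*Protocol article*

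**What the plan says.** All references are to the protocol article.

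- **Study Design** sets the end of follow-up: "Follow-up will be conducted at baseline, 4 weeks after treatment, and every 8 weeks afterward until disease progression or death". The same sentence adds that evaluation follows RECIST 1.1.
- **Outcomes** gives imaging its own sentence with the same stop. CT or MR "will be used to assess the tumor at baseline, 4 weeks after treatment, and every 8 weeks afterward until disease progression or death".
- **Secondary Outcomes** lists OS first, "calculated as the time from randomization to death due to any cause". Its censoring rule reads: "For subjects who are lost to follow-up before death, the time of the last follow-up is used as the time of no death".
- **Statistical Analysis** fixes the method: "PFS and OS will be illustrated by the Kaplan–Meier survival curve and compared between groups using the log-rank test".
- **Drop-Out Criteria** is the only place shown that extends observation past a stop, and it covers safety only: "The investigators will continue to evaluate the safety after they have been dropped out".

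**The concern.** Two stated rules do not fit together. Follow-up has one stated end, the earlier of progression and death. OS needs observation up to death, and in this disease death usually comes after progression. The article's own figures show the gap: it expects a control-group median PFS of 18 months (Sample Size), and the trial of first-line osimertinib that it cites reported that "its first-line treatment significantly prolongs OS to 38.6 months" (Discussion).

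If sites apply the Study Design sentence as it stands, the last follow-up of a progressing patient is the progression visit, and the OS rule then supplies that date as the censoring time. Kaplan-Meier and log-rank require that censored patients have the same later risk of death as those who stay under observation. Patients censored because they have just progressed do not. If YYJD delays progression, the amount and timing of this censoring would also differ between the arms. What would be reported as OS would then be close to time to death without prior progression.

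**Working it through.** The article gives no expected number of deaths and no power for OS, so there is no plan figure to reproduce. The 314 patients are taken as given. Whether that number suits the PFS comparison is a separate question.

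**Inputs from the article**
- 314 patients, 157 per arm; accrual R = 18 months, total T = 30 months; censoring 1% per month; median PFS 18 and 23 months (Sample Size).
- Median OS 38.6 months (Discussion).

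**Assumptions**
- Exponential PFS and OS, uniform accrual, and a median OS of 38.6 months in both arms.
- q, the share of PFS events that are deaths without documented progression. The article does not give it; 5% to 20% is shown.

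**Formula.** With event hazard λ = ln 2 / median, loss hazard γ = −ln 0.99 = 0.01005 (or 0) and s = λ + γ:

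P(event seen) = (λ/s) × [1 − (e^(−s(T−R)) − e^(−sT)) / (sR)]

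**Step 1: deaths observable if survival is followed past progression.** λ = 0.6931/38.6 = 0.01796.
- Without loss: 1 − (0.8062 − 0.5835)/0.3232 = 0.311, and 314 × 0.311 = about 98.
- With loss, s = 0.02801: 0.6412 × [1 − (0.7146 − 0.4316)/0.5041] = 0.281, and 314 × 0.281 = about 88.

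**Step 2: PFS events by month 30, with loss.**
- Control: λ = 0.03851, P = 0.498, 157 × 0.498 = about 78.
- Intervention: λ = 0.03014, P = 0.420, 157 × 0.420 = about 66.
- Total: about 144. The gap between 78 and 66 shows how stopping at progression would act unequally on the arms if the design assumption is true.

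**Step 3: deaths seen if observation stops at progression.** Deaths seen = q × 144.

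| q (assumed) | Deaths seen | Share of the 88 |
|---|---|---|
| 5% | 7 | 8% |
| 10% | 14 | 16% |
| 15% | 22 | 24% |
| 20% | 29 | 33% |

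Half of the deaths are seen when q = 44.2/144.2 = about 31%. Without loss there are about 158 PFS events and 98 deaths, and half is again reached at about 31%.

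**Step 4: sensitivity to calendar time.** Trial Status gives recruitment from January 2021 to December 2022, about 24 months. With R = 24 and an assumed T = 36, observable deaths are about 97 to 108 and PFS events with loss about 155. For q = 5% to 20%, about 8 to 31 deaths are seen, or 8% to 32% of the 97. The threshold is unchanged at about 31%.

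**Step 5: sensitivity to the shape of OS.** A constant death hazard from randomisation puts more deaths early than a course in which most deaths follow progression. As a check, let survival be S(t) = e^(−λt) + (1 − q)λ(e^(−μt) − e^(−λt))/(λ − μ). Here λ is the PFS hazard of each arm and μ the death hazard after progression, solved so that S(38.6) = 0.5. With R = 18, T = 30 and 1% monthly loss, about 67 deaths (q = 5%) to 73 deaths (q = 20%) are observable. The share seen is 7.2/66.8 = 11% to 28.8/72.7 = 40%, and half is reached at q of about 26%. The counts shift, but over this range of q most deaths are still missed.

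**The case against.** A reader might infer that OS in this trial is in fact censored at progression and that most deaths will never be recorded. The article does not support that as a statement of fact, for four reasons.

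- No section says that OS is censored at progression. The censoring rule is confined to patients lost before death, and a patient with documented progression is not thereby lost. Read alone, the OS definition implies an intention to follow patients to death.
- The Study Design sentence refers to RECIST, and Secondary Outcomes ties performance status, quality of life and laboratory tests to the imaging visits. The sentence can be read as the visit schedule, which may properly stop at progression while vital status is still collected.
- The flow diagram and the schedule of assessments are not shown, nor are the full protocol and the analysis plan. Any of them may provide for survival contact, and an article may leave such detail to them.
- The loss of deaths cannot be given as one percentage, because q is not in the article.

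These objections limit how firmly the point can be put, but they do not remove it. The article does more than stay silent: it states an end of follow-up, apart from the imaging rule, and that end conflicts with the endpoint. If survival follow-up exists elsewhere, Study Design misstates it. If it does not, OS cannot be estimated as defined. The text needs correcting in either case.

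**Conclusion.** The conflict between the stated end of follow-up and the OS endpoint is real and should be reconciled. Under the literal reading, censoring is informative and the planned OS analysis would not estimate OS. The number of deaths seen by month 30 would fall from about 88 to 98 to about 7 to 29. Those counts rest on exponential times, a median OS of 38.6 months in both arms, the 18/30-month design, and an assumed 5% to 20% of PFS events being deaths without progression. The conclusion that most deaths would be missed fails only if that share exceeds about 31%, or about 26% under the alternative survival shape. Whether sites will apply the literal reading cannot be settled from the article.

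The consequence is confined to OS, a secondary outcome. The sample size is based on PFS, and the primary PFS analysis is not affected.

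**What to change.** Reconcile Study Design, Outcomes and the OS definition with three statements:

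1. The stop at progression applies to the visit and imaging schedule only.
2. After progression or the end of study treatment, vital status is collected for all randomised patients, at a stated interval, by telephone contact or record check, until the data cut-off.
3. OS is censored at the date last known alive, for every patient not known to have died by the cut-off.

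If the full protocol already provides for this, correcting the published wording and confirming that sites follow the full text is enough.

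The cost is a short amendment and a small added workload for existing site staff. The change concerns data collection only. It is easiest to make early: Trial Status reports 58 of 314 patients enrolled by 23 December 2021, and vital status is harder to recover once patients have left follow-up.

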**FIGURE 1 F1:**
[figure not shown]
The flow diagram of the study.

### Participants

Participants will be recruited through the outpatient and inpatient wards of the eight sites. Posters and digital media will be used for recruitment.

#### Inclusion Criteria

(1) Pathologically confirmed NSCLC (Health Commission of PRC and National Health Commission of the People’s Republic of China, 2019).(2) Locally advanced or metastatic NSCLC that is not amenable to curative surgery or radiotherapy.(3) The tumor has one of 2 common EGFR mutations known to be associated with EGFR-TKI sensitivity (Ex19del, L858R).(4) Patients must have no treatment for locally advanced or metastatic NSCLC.(5) Aged 18–74 years old.(6) No major organ dysfunction: hemoglobin ≥120 g/L, absolute neutrophil count (ANC) ≥1.5 × 10^9^/L, platelets ≥80 × 10^9^/L, bilirubin ≤ 1.5ULN, alkaline phosphatase (AP), aspartate aminotransferase (AST), and alanine aminotransferase (ALT) ≤ 2.5 × ULN. INR ≤ 1.5, creatinine ≤ 1.5 × ULN.(7) Provision of informed consent forms.

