#### Exclusion Criteria

(1) Those with a history of other malignancies within 5 years;(2) Those with symptomatic brain metastases;(3) Those with congestive heart failure (> class II NYHA heart function), unstable (angina at rest), initial onset (starting within 3 months), angina pectoris, or myocardial infarction occurring within 6 months;(4) Those with active infection (> Grade 2 adverse events according to CTCAE.5.0 version);(5) Those with a history of uncontrollable mental illness.

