### Sample Size

The sample size was calculated by the statistician of the Clinical Evaluation Center of Shanghai University of Traditional Chinese Medicine by the Power Analysis and Sample Size (PASS) 14 software. PFS is the primary endpoint. According to our previous study, the median PFS of the control group is expected to be 18 months and that of the intervention group is expected to be 23 months, with a recruitment duration of 18 months and a total duration of 30 months. The two groups were allocated in a ratio of 1:1. Given that *α* = 0.05, *β* = 0.20, considering that the average monthly censored rate is 1%, the total sample size is 314 cases, 157 cases in each group.

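### The prior-therapy criterion bars only treatment for advanced disease, so patients relapsing on or soon after a (neo)adjuvant EGFR-TKI can enter a first-line osimertinib trial

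*Protocol article*

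**What the plan says.** All references are to the protocol article.

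- **Inclusion Criteria.** The rule on earlier treatment is "4) Patients must have no treatment for locally advanced or metastatic NSCLC". Criterion 2 requires "Locally advanced or metastatic NSCLC that is not amenable to curative surgery or radiotherapy", which a relapse after earlier resection can satisfy. Criterion 3 is "The tumor has one of 2 common EGFR mutations known to be associated with EGFR-TKI sensitivity (Ex19del, L858R"; it sets no condition on earlier TKI exposure or on resistance mutations.
- **Exclusion Criteria.** There are five items. The list opens with "1) Those with a history of other malignancies within 5 years;(2) Those with symptomatic brain metastases" and goes on to cardiac disease, active infection and mental illness. None concerns earlier EGFR-TKI, other earlier systemic therapy, or time since such therapy.
- **Abstract.** Patients are enrolled "if they are ready to take osimertinib as first-line treatment, aged 18–74 years old, and provide signed informed consent".
- **Sample Size.** PFS planning assumes that "the median PFS of the control group is expected to be 18 months and that of the intervention group is expected to be 23 months".
- **Randomization and Statistical Analysis.** The allocation factors are gender, age group and center. Prior TKI exposure is not among them, nor is it a named covariate in the adjusted Cox model. That model lists a covariate for EGFR-TKI drugs, but every patient takes osimertinib and the article does not say that the term means earlier exposure.

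**The concern.** A patient resected for early-stage EGFR-mutated disease who relapses on an adjuvant EGFR-TKI, or soon after stopping it, has had no treatment for advanced disease. If the tumour still carries Ex19del or L858R, the patient can meet every listed criterion. Yet the trial asks whether the herbal decoction (YYJD) delays acquired resistance to osimertinib given first line, and such a patient may already have progressed under the same drug class. If the earlier drug was osimertinib, the study treatment would be a re-challenge.

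The stakes are interpretive. The first-line conclusion would rest on a mixed population, the control median could fall below its planning value, and any YYJD effect could be diluted if it is weaker in these patients.

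**Working it through.** **1. Reading the criteria together.** Take a patient who relapses with unresectable disease after surgery and an adjuvant EGFR-TKI for stage I or II disease.

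- Criterion 2 (stage now): met.
- Criterion 3 (mutation): met if Ex19del or L858R persists.
- Criterion 4 (no treatment for advanced disease): met, because the TKI was given for earlier-stage disease.
- Five exclusions: none applies.

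For resected stage III disease, one site could count the adjuvant TKI as treatment for locally advanced NSCLC and exclude the patient, while another might not. The Abstract's first-line condition does not settle either case, because the first treatment given for advanced disease can still be called first-line after adjuvant therapy.

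**2. What the planning figures describe.** The Discussion says "the median PFS of patients treated with osimertinib is as high as 18 months" in a paragraph on first-line use. It also reports a 5-month gain in median PFS for YYJD with first-generation TKIs as first-line treatment. The planned medians of 18 and 18 + 5 = 23 months match these figures. Sample Size itself credits only the group's own earlier study.

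**3. The plan's own numbers.** With exponential PFS, HR = 18/23 = 0.783 and ln HR = -0.2451. Schoenfeld events for two-sided 5% and 80% power are 4 × (1.960 + 0.842)² / 0.2451² = 523. With uniform accrual over 18 months, 30 months in total and 1% monthly censoring, the event probabilities are 0.498 (control) and 0.421 (YYJD). The 314 patients then give 314 × 0.459 ≈ 144 events. The stated 314 is therefore not reproduced for 80% power. That is a separate matter, and nothing here depends on it.

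**4. Sensitivity under assumed values.** The document gives neither the share f of exposed patients nor their PFS on osimertinib. Assume f = 2%, 5% or 10% and a control-arm median m of 6 to 10 months in that subgroup. The overall control median t solves

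(1 - f) × 2^(-t/18) + f × 2^(-t/m) = 0.5.

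Check at f = 0.05, m = 6, t = 17.03: 0.95 × 0.519 + 0.05 × 0.140 = 0.493 + 0.007 = 0.500.

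To bound the dilution, suppose YYJD has no effect at all in exposed patients, and average ln HR by share of events. At f = 0.05, m = 6, about 150.2 events are expected, of which 0.95 × 144.2 = 137.0 come from unexposed patients. The average ln HR is (137.0/150.2) × (-0.2451) = -0.2236, so HR = 0.80 and 628 events are needed.

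| Assumed f | Control median, months (m = 6 to 10) | Average HR if no effect in exposed | Events needed if no effect | Events needed if same HR |
|---|---|---|---|---|
| 0 | 18.0 | 0.783 | 523 | 523 |
| 2% | 17.6-17.8 | about 0.79 | 556-563 | 523 |
| 5% | 17.0-17.5 | about 0.80 | 609-628 | 523 |
| 10% | 16.1-16.9 | 0.81-0.82 | 713-757 | 523 |

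If the HR is the same in exposed patients, this averaging leaves the requirement at 523 and events arrive slightly sooner.

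**The case against.** **Omission rather than error.** Criterion 4 agrees with a literal reading of first-line, no statement contradicts it, and protocol v2.0 is not shown. In part this stands: the full protocol may say more. But the article prints numbered lists that look complete, and criterion 4 addresses earlier treatment in explicit words. The point is what that stated rule admits.

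**T790M.** A reader might infer from the Discussion's remark that patients on EGFR-TKIs "will inevitably experience treatment failure due to secondary drug resistance, and more than 50% of them have the T790M mutation" that anyone with earlier TKI failure enters already resistant to the study drug. The document does not support this. It goes on to say that osimertinib solved that problem and overcomes T790M, so a patient relapsing after a first-generation TKI could still respond and later acquire resistance on study. The mechanisms it lists for osimertinib resistance (C797S, MET amplification) bear on earlier osimertinib, which is the narrower and clearer case.

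**Planning population.** It is tempting to say that the 18 months describes TKI-naive patients. The article never uses that term, and the eligibility rules of the cited trial are not shown. Only the match with first-line figures can be claimed.

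**Size.** The share, the subgroup median and the absence of a YYJD effect have no anchor in the document. This stands in full: at 2% exposure the shift in the control median is negligible.

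**Imbalance.** Any factor outside gender, age and center can be unbalanced by chance. Randomisation still gives a valid comparison, so no bias should be inferred.

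**Conclusion.** The concern holds in a limited form. The printed criteria admit patients who relapse on or soon after a (neo)adjuvant EGFR-TKI and are ambiguous for resected stage III disease. This sits badly with a first-line question about delaying acquired resistance, above all after earlier osimertinib. The consequence is a mixed population and possible dilution, not an invalid comparison. Its size is unknown: under the assumed subgroup medians, the control median moves by 0.2 to 0.4 months at 2% exposure and by 1.1 to 1.9 months at 10%. More events are needed only if YYJD works less well in these patients. The article does not say whether any such patient has been enrolled, and none should be presumed.

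**What to change.** Amend criterion 4 so that it also covers prior EGFR-TKI given in any setting, in line with the first-line question; this also settles resected stage III disease for earlier TKI use. Any interval for non-TKI (neo)adjuvant therapy is for the investigators to set, as the document offers no figure for one. For patients already enrolled, record prior EGFR-TKI exposure and add a PFS sensitivity analysis that leaves out those exposed.

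The cost is one amended sentence, one data item and one extra analysis. Trial Status reports 58 of 314 patients enrolled by 23 December 2021, so at that date 314 - 58 = 256 could still have been recruited under the clarified rule. The downside is that a small number of relapsed patients become ineligible.
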